## Abstract

Background: Propofol, ketamine, and sufentanil are the most commonly used anesthetics during bronchoscopy, alone or in combination, for sedation. Esketamine is an s-enantiomer of ketamine racemate and has both sedative and analgesic effects. Esketamine does not inhibit respiration and maintains hemodynamic stability. This study aims to compare the clinical efficacy of esketamine/propofol with sufentanil/propofol for patients during bronchoscopy. Methods: Patients undergoing bronchoscopy will be randomly assigned to receive either sufentanil/propofol (sufentanil group; *n* = 33; sufentanil: 0.2 μg/kg) or esketamine/propofol (esketamine group; *n* = 33; esketamine: 0.2 mg/kg) for sedation and analgesia. Intraoperative clinical information, general anesthetic drug dosage, the incidence of intraoperative hypoxemia, total time of hypoxemia, awakening time, delirium, nausea and vomiting, adverse reactions, and patient satisfaction will be collected. Discussion: Hypoxia has detrimental effects on patients with respiratory disease. Ameliorating hypoxemia in patients undergoing bronchoscopy is critical. Our results will provide effective sedation with esketamine in patients undergoing bronchoscopy. Trial registration: Chinese clinical trial registry: ChiCTR2200058990.

## 1. Background

Bronchoscopy has been an important tool in the evaluation and management of respiratory disease for many years [1,2,3]. It is a complicated, highly stimulating, painful, and irritating operation performed in patients with pulmonary disease, with a relatively high risk of hypoxemia, coughing, wheezing, and dyspnea [4,5,6]. Intraprocedural sedation, local anesthesia, and general anesthesia have been implemented to avoid such problems in patients undergoing bronchoscopy [7,8,9,10]. Because any movement of the patient could importantly affect the success of the bronchoscopy and because of the great suffering caused to the patient, procedures are usually performed under deep sedation or even general anesthesia.

The combination of propofol and an opioid is a usual anesthesia method during bronchoscopy, despite known side effects such as hypoxemia, postoperative nausea and vomiting, etc., especially for patients without airway devices [11,12]. Joskova et al. found in animal experiments that pharmacodynamic interactions between propofol, sufentanil, and midazolam via GABA_A_ receptor-mediated interactions negatively affect ciliary beat frequency in respiratory epithelial cells [13]. Analgesia and sedation are key for successfully performing bronchoscopy. Opioids may be preferred in combination with other sedative medications to improve patient tolerance during bronchoscopy [14]. In addition to the risk of respiratory depression, opioids have also been reported to cause acute exacerbation of asthma [15]. The sedation used in bronchoscopy requires a rapid onset of action, a short duration of action, rapid recovery, and few adverse effects. Minimizing these risks is therefore an important objective in making sedation surgery safer.

Esketamine, the s-enantiomer of ketamine racemate, has a higher affinity for the NMDA receptor than the r-enantiomer. Hengrui Medicine Co., Ltd. completed the preclinical study of esketamine three years ago and received the clinical study approval from the state food and drug administration [16]. Esketamine combines sedative and analgesic functions. Additionally, its sympathomimetic properties counteract the hemodynamic depression of propofol, thus reducing the risk of cardiovascular and respiratory depression. Due to the increased sympathetic tone, voluntary breathing and airway reflexes are maintained and hypotension is uncommon. Low-dose esketamine not only reduces opioid consumption but also stabilizes breathing, which is evidenced by Jonkman et al. [17]. They showed that esketamine countered respiratory depression by increasing remifentanil-reduced ventilator CO_2_ chemosensitivity.

Esketamine also maintains intraoperative hemodynamic stability. Tu et al. found that esketamine improved hemodynamics, reduced surgical stress and inflammatory response, and promoted postoperative cognitive recovery compared to sufentanil [18]. Esketamine is commonly used for bronchoscopy in children, which is beneficial for patient sedation and reducing the incidence of delirium [19]. Esketamine relaxes bronchiolar muscles and inhibits bronchial constriction due to histamines, thereby reducing tracheal and bronchial muscle spasms.

Endoscopic treatment is now widely used as an effective method to diagnose or treat lung diseases and mainly includes rigid or flexible bronchoscopes. These interventions are high-risk and pose a great challenge to the anesthesiologist. How to establish an appropriate gas exchange to sustain the patient and allow for a smooth operation is an issue to be considered during anesthesia. In addition, reducing perioperative complications, such as intraoperative hypoxemia, airway spasm, and choking, remains an important consideration for the anesthesiologist. Many patients have hypoxia or symptoms of dyspnea before bronchoscopy. In the experience with bronchoscopy at our hospital, we noticed that oxygen saturation (SpO_2_) decreased in many patients who experienced general anesthesia without intubation when undergoing bronchoscopy, despite continuous inspired oxygen.

Hypoxemia is the most frequent complication, and the risk in patients undergoing this procedure is approximately 26–69.1%, due to the different choices of anesthesia and inconsistent indicators for evaluating hypoxemia [12,20,21,22,23,24,25]. Many patients could not tolerate a bronchoscopic procedure without sedation for anxiety and intense stimulation. While the frequently reported regimens include an opioid/propofol combination, other authors [26,27] have suggested that esketamine may be both safe and effective for short surgery. Although previous studies on the safety and validity of esketamine in bronchoscopy are scarce, several studies have demonstrated the effectiveness of ketamine in bronchoscopy, especially for pediatric patients [28,29]. Low-dose intravenous ketamine reduces perioperative opioid use and may provide postoperative analgesia for patients [30]. So far, there is only limited evidence on whether esketamine can decrease the incidence of hypoxemia and improve anesthetic outcomes in patients undergoing bronchoscopy compared with sufentanil or even enhance recovery after surgery.

Data from prospective randomized trials on the effects of esketamine- and sufentanil-assisted general anesthesia on anesthetic awakening are scarce. There is still little evidence of combined esketamine/propofol in bronchoscopy, and it is still open to discussion whether esketamine or sufentanil could reduce the incidence of intraoperative hypoxemia. In our hospital, bronchoscopy has been performed under local anesthesia or sedation with propofol combined with sufentanil by anesthesiologists. On this account, we conducted a randomized controlled trial in this high-risk population to investigate whether opioid-free anesthesia could reduce perioperative hypoxemia. The current study aims to evaluate the efficacy and safety of esketamine/propofol compared with the sufentanil/propofol regimen. We hypothesized that the use of esketamine in patients undergoing flexible bronchoscopy would result in a lower incidence of hypoxemia than standard sufentanil methods.

## 2. Methods/Design

### 2.1. Trial Design

We prepared the study, including ethics approval and pilot testing, which lasted about 3 months. Formal subject recruitment began on 9 March 2022 and is anticipated to be completed by 30 August.

The study is being conducted in Beijing Chao-Yang Hospital, Capital Medical University. The study is designed as a prospective, randomized, controlled, single-trial that includes 66 patients undergoing flexible bronchoscopy and is reported following the Standard Protocol Items: Recommendations for Interventional Trials (SPIRIT) statement [31]. Ethics approval was obtained from the Ethics Committee of the Beijing Chao-Yang Hospital, Capital Medical University on 8 March 2022. The study will be performed following the Declaration of Helsinki [32] and is registered in the clinical trials (22 April 2022, 2022; Clinical Trial: ChiCTR2200058990). Written informed consent is obtained from all participants who meet the inclusion criteria. The present study meets the requirements of the Consolidated Standards for Trial Reporting (CONSORT) checklist. This study is based on a flowchart (Figure 1). Randomization is performed using the Randomization online version software (Table 1).

Potential participants undergoing bronchoscopy are screened for eligibility criteria. All enrolled patients are randomly divided into either the esketamine (Jiangsu Hengrui Pharmaceutical Co., Lianyungang, China) group or the sufentanil (Yichang Humanwell Pharmaceutical Co., Ltd., Yichang, China) group at a 1:1 ratio. We divide the patients into the esketamine group (receives esketamine/propofol sedation) or the sufentanil group (receives propofol/sufentanil sedation) during bronchoscopy. Standard deep sedation with propofol (Fresenius Kabi AB, [name]) target-controlled infusion (TCI) is provided by an anesthesiologist in both groups.

### 2.2. Recruitment and Eligibility Criteria

A special researcher assesses patient eligibility one day before bronchoscopy. The eligible patient, according to the inclusion and exclusion criteria, who agrees to participate in this study is enrolled and randomly assigned to receive either esketamine/propofol- or sufentanil/propofol-based intravenous sedation. The research is canceled in situations where there are patients with serious cardiovascular accidents or who die in the perioperative period.

### 2.3. Inclusion Criteria

Aged 18 years or older at the time of participation.Planning for elective bronchoscopy under general anesthesia without intubation.American Society of Anesthesiologists (ASA) classification I–III.

### 2.4. Exclusion Criteria

Less than 18 years old at the time of participation.SpO_2_ less than 90% after preoperative oxygenation.History of depression or taking antidepressants.History of neuropsychiatric disorders or drug abuse.Inability to cooperate with the scale assessment.Abnormal liver and kidney function.History of hyperthyroidism.Serious adverse reactions such as cardiac arrest and cardiopulmonary resuscitation during bronchoscopy.Severe hypertension, intraocular pressure, or intracranial pressure.A history of allergy to the study drugs or to eggs or soybeans.

### 2.5. Randomization and Blinding

Patients are randomly allocated to the esketamine group or the sufentanil group. A computer-generated randomization schedule is conducted to randomly assign included patients in a 1:1 ratio to reach double-blind treatment with either esketamine or sufentanil. Randomly permuted blocks are used for randomizing and are performed by a trained nurse who specializes in research. The nurse will utilize sealed opaque envelopes to reveal the treatment group on the morning of the operation. Esketamine and sufentanil are both colorless and transparent with 1 mL each. The esketamine or sufentanil is diluted to 10 mL with 0.9% saline by an anesthesia nurse on the day of bronchoscopy. The patients, anesthesiologists, investigators, those assessing the outcomes, and those analyzing the data are blind to the treatment assignment.

### 2.6. Bronchoscopic Procedures

Indication for bronchoscopy includes infection, lung cancer, hemoptysis, interstitial lung disease, and others. The specific type of bronchoscopic procedures is determined by the respiratory surgeon, mainly according to the patient’s diagnosis, preoperative CT scan of the lesion location, size, cancer stage, etc. The types of procedures include inspection with bronchoscopic biopsy, inspection with bronchoalveolar lavage (BAL), bronchial washings, transbronchial lung biopsy (TBLB), conventional transbronchial needle aspiration (TBNA), endobronchial biopsy (EBB), and inspection only.

### 2.7. Anesthetic Management

Bronchoscopy is performed in the outpatient bronchoscopy room. All patients fast from food and water for 8 h before bronchoscopy. Preoxygenation is applied 5 min before anesthesia induction. General anesthesia is performed by anesthesiologists. All patients are monitored by noninvasive blood pressure, electrocardiography, and pulse oximetry and infused with 500 mL NaCl 0.9% at the rate of 250 mL/h. All patients receive oxygen administration (3–6 L/min via a nasal cannula) during the bronchoscopy. After preoxygenation with 100% oxygen, sufentanil (0.2 μg/kg) and propofol (1.5–2.5 mg/kg) are administered during the induction of anesthesia in the sufentanil group or propofol (1.5–2.5 mg/kg) and esketamine (0.2 mg/kg) in the esketamine group. Endoscopic examination starts after the patient has no obvious physical activity and the eyelash reflex has disappeared. Simultaneously, general anesthesia is maintained with propofol at a dose of 4–12 mg kg^−1^ h^−1^. The surgeon injects 5 mL of 2% lidocaine (Tianjin Jinyao Pharmaceutical Co., Tianjin, China) through the tracheoscope into the trachea after the tracheoscope enters the glottis. An amount of 0.5 mg/kg propofol will be added if the swallowing reflex, obvious body motion, or choking response is observed. For patients undergoing transient episodes of SpO_2_ below 90%, high fresh oxygen will be used first to obtain sufficient ventilation and to compensate for airway leaks. If this does not work, we will give the patient mandibular support. If none of these works, we will ask the performer to remove the placed bronchoscope and ventilate the patient for a few minutes until the SpO_2_ rises above 95% and then restart the procedure. In this study, it takes approximately 20 min to perform a bronchoscopy examination, and no additional muscle relaxants or tracheal intubation will be added. Intraoperative vasopressors will be administered to maintain mean arterial blood pressure within 20% of the baseline measurement. Propofol is discontinued at the end of the procedure.

Heart rate (HR), SpO_2_, and noninvasive blood pressure (NIBP) are measured by an independent, blinded observer who collects research data at 3 min intervals. Patients are moved to the postanesthesia care unit (PACU) with oxygen support to maintain the oxygen saturation above 92%. Patients will be transferred to the PACU for Aldrete, delirium, and postoperative nausea and vomiting (PONV) assessment after awakening. The modified Aldrete score is used to assess the recovery from anesthesia and the return of psychotomotoric fitness. This validated assessment consists of 5 aspects (activity, respiration, blood pressure, consciousness, and SpO_2_), with a total score of 10. The clinical data on preoperative diagnosis, type of combined lung disease and blood gas, duration of bronchoscopy, and length of hospital stay are extracted from the medical record.

Safety will be assessed by interview and adverse event (AE) monitoring. All adverse events occurring during the whole study are recorded. Further follow-up is also necessary if there are clinical abnormalities.

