### 2.9. Primary Objective

The primary endpoint of the study—the effect of esketamine versus sufentanil on the incidence of intraoperative hypoxemia—is the rate of SpO_2_ < 90 lasting for the 30 s during the bronchoscopy.

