### 2.10. Secondary Objectives

Hemodynamic stability and safety (cardiovascular adverse events such as hypotension or bradycardia, which are measured as a change >25% from baseline and/or necessitating an intervention).

Time from end of bronchoscopy to Aldrete score of 9 (quality of awakening). This is defined as the time for a patient to return to full consciousness from sedation (Aldrete score of 9) after drug administration ceases, which should be accurate on a minute time scale).

Severe intraoperative hypoxemia (SpO_2_  <  75% at any time).

The total duration of intraoperative hypoxemia (total duration of SpO_2_ < 90%).

Incidence and score of PONV at the end of the operation and 1 day after the operation (Likert scale, classified as none, mild, moderate, and severe) [33].

Incidence of delirium within 3 days after bronchoscopy (to the evaluation of a patient’s delirium status and assessment by The Confusion Assessment Method (CAM)).

Incidence of postoperative fever.

Patient satisfaction (one day after the procedure patients will be visited to assess post-procedural satisfaction using the world SIVA International Sedation Task Force Tool [34]. (0 = very unsatisfied, 1 = unsatisfied, 2 = satisfied, 3 = very satisfied).

Propofol dosage in both groups.

The examination time.

The types of procedures.

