## Figures and Tables

**Figure 1 jcm-11-04587-f001:**
[figure not shown]
Study enrollment. SpO_2_, oxygen saturation; PONV, postoperative nausea and vomiting.

**Table 1 jcm-11-04587-t001:** Flow chart of the study. PACU, postanesthesia care unit; POD, postoperative day; CAM, the Confusion Assessment Method; PONV, postoperative nausea and vomiting. “×” means perfoming in that time.

Items	Visit 1	Visit 2	Visit 3	Visit 4	Visit 5
Time	One day before bronchoscoy	Morning of bronchoscopy	During bronchoscopy	PACU	POD1
Eligiblility screen	×				
Medical history and medication history	×				
Surgery history	×				
Physical examination	×				
Inclusion/exclusion criteria	×	×			
Informed consent		×			
Randomization		×			
Demographics			×	×	
Hemodynamic variables			×	×	
Study drug			×	×	
Outcome indicators			×	×	×
CAM				×	×
Aldrete				×	
PONV				×	×
Adverse events			×	×	×
Patient satisfaction					×

**Table 2 jcm-11-04587-t002:** Definitions of the multiple outcomes included in this study protocol. SpO_2_, oxygen saturation; PONV, postoperative nausea and vomiting.

Outcome	Definition	Instrumental/Tool
Incidence of intraoperative hypoxemia	The rate of SpO_2_ < 90% lasts for 30 s during the bronchoscopy.	SpO_2_
Hemodynamic stability and safety	Cardiovascular adverse events such as hypotension or bradycardia, which will be measured as a change >25% from baseline and/or necessitating an intervention.	Non-invasive blood pressure and electrocardiogram
Awakening time	Time from end of bronchoscopy to Aldrete score of 9.	Aldrete
Severe intraoperative hypoxemia	SpO_2_ < 75% at any time during the bronchoscopy.	SpO_2_
Total duration of intraoperative hypoxemia	Total duration of SpO_2_ < 90% during the bronchoscopy.	SpO_2_
PONV	The severity of PONV (none, mild, moderate, and severe).	Likert scale
Delirium	To evaluation of a patient’s delirium status within 3 days after bronchoscopy.	The Confusion Assessment Method
Adverse events	Accidental or adverse reactions to sedatives that threaten or cause patient injury or discomfort	World SIVA International Sedation Task Force Tool
Patient satisfaction	Patient satisfaction with the procedure experience (very unsatisfied, unsatisfied, satisfied, very satisfied)	Likert scale

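### The only stated SpO2 recording schedule, one reading every 3 minutes, does not match the 30-second primary endpoint or the duration and nadir endpoints

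*Protocol article*

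**What the plan says.** On data collection, section 2.7 states: "Heart rate (HR), SpO_2_, and noninvasive blood pressure (NIBP) are measured by an independent, blinded observer who collects research data at 3 min intervals". SpO2 is named in that sentence, and no other recording interval, data export or event log for SpO2 appears in the article. The same section says that every patient has pulse oximetry and that "it takes approximately 20 min to perform a bronchoscopy examination".

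Three endpoints depend on SpO2:

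- **Primary** (section 2.9): it "is the rate of SpO_2_ < 90 lasting for the 30 s during the bronchoscopy". Table 2 repeats the time criterion ("lasts for 30 s during the bronchoscopy") and names the tool only as SpO2.
- **Duration** (section 2.10): "The total duration of intraoperative hypoxemia", meaning cumulative time below 90%.
- **Severe hypoxemia** (section 2.10 and Table 2): any value below 75% during the procedure.

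Section 2.7 also describes a stepwise response to desaturation: "For patients undergoing transient episodes of SpO_2_ below 90%, high fresh oxygen will be used first".

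**The concern.** The stated interval is 180 s and the primary criterion is 30 s, a ratio of six. A spot value shows that SpO2 was low at one moment. It does not show how long SpO2 had been low, how long it stayed low, or how far it fell between readings. All three endpoints need exactly that information.

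If the 3-min sheet were the source, short episodes would often go unrecorded. A single low reading would then have to be called an event or a non-event without evidence of its length. Classification would depend partly on where the 3-min clock fell. Missed events at the same rate in both arms shrink the risk difference, and the trial has only 33 patients per arm.

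**Working it through.** **Inputs from the article.** Recording interval 180 s and procedure of about 20 min (section 2.7). Primary criterion 30 s (section 2.9). Pilot incidences 64% and 30%, 5% significance, 80% power, 10% drop-out and 33 per arm (section 2.11). Two-sided testing (section 3.4).

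**The plan's own figure.** With unpooled variance, n = (1.96 + 0.8416)² × (0.64 × 0.36 + 0.30 × 0.70) / 0.34² = 7.849 × 0.4404 / 0.1156 = 29.9, so 30 per arm. Then 30 × 1.1 = 33, as stated. The sample size is not in dispute here.

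**What the readings can show.**

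- Number of readings: 20 / 3 = 6.7, so 6 or 7 per patient.
- One reading below 90% between two at or above 90% fits an episode of any length from a few seconds to just under 2 × 180 = 360 s. It cannot establish 30 s.
- Two consecutive low readings do not establish it either, since SpO2 may have recovered in between.
- Cumulative time below 90% is known only in steps of about 3 min.
- A fall below 75% that lasts 30 s is missed with probability 1 − 30/180 = 83%.

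**Chance that an episode meets a reading.** For one episode of d seconds at random phase, the probability is min(1, d/180). For three independent episodes of the same length it is 1 − (1 − d/180)³. Episode lengths are not in the article, so the range is an assumption.

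| d | one episode | three episodes |
|---|---|---|
| 30 s | 17% | 42% |
| 60 s | 33% | 70% |
| 90 s | 50% | 88% |

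A single episode of 180 s or more is always met.

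**Illustration of power.** Let a fraction c of true events be captured, equally in both arms and with no false positives. Take 64% and 30% as the true rates. The table gives exact power of the Pearson χ² test by binomial enumeration.

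| c | observed rates | power, 33 per arm | power, 30 per arm |
|---|---|---|---|
| 1.0 | 64% vs 30% | 84% | 77% |
| 0.7 | 45% vs 21% | 56% | 50% |
| 0.5 | 32% vs 15% | 38% | 34% |

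The normal approximation agrees closely: 80% at full capture and 37% at half capture, with 33 per arm.

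**The case against.** The strongest reply is that the 3-min sentence describes a routine vital-signs sheet covering heart rate, SpO2 and blood pressure together, and that the endpoints are captured in another way. Several passages support this. Oximetry runs on every patient. A response to transient desaturation requires someone to watch the monitor between readings. A blinded observer is present. Table 1 lists outcome indicators and hemodynamic variables in separate rows. An article may also leave case-report-form detail to the full protocol.

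Much of this stands. A reader might infer that the three endpoints cannot be determined at all from what the trial collects. The documents do not support that, because they neither say that the endpoints come from the 3-min readings nor rule out another record. The reply does not remove the point, however. A monitor on display is not a data record, and the article does not say that the trace is stored or that episodes are timed. What it does state for SpO2 is an interval six times the primary criterion. That is a rule fixed badly rather than a detail left out.

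A reader might also take 56% or 38% as the trial's real power. The documents do not support that either. The capture fractions are assumed, and repeated or long episodes raise capture. The article does not say how the pilot measured SpO2. If the pilot used the same 3-min readings, 64% and 30% already contain the missed events, and diluting them again would count the loss twice.

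Finally, a reader might argue that rescue begun before 30 s misclassifies patients. Under the stated definition, a desaturation corrected within 30 s is a non-event, and the same steps apply in both arms under blinding. This supports an optional sensitivity analysis and nothing more.

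**Conclusion.** The point holds as a mismatch within the article. The only stated SpO2 recording schedule is too coarse for the primary endpoint and for two secondary endpoints. Followed as written, readings 180 s apart cannot yield 30 s of persistence, total time below 90% or the nadir.

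The consequence is conditional. If no other SpO2 record is used, events will be missed and misclassified in both arms, with capture of 17% to 50% for a single episode of 30 to 90 s and 42% to 88% for three independent ones. The power loss cannot be stated. The fall from 84% to 56% assumes 70% capture and pilot rates measured with full capture, and neither is documented. Even if the pilot rates were already diluted, the validity problem would remain, because a spot value does not show that the 30 s criterion was met.

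**What to change.** In sections 2.7 and 2.9, state that the three SpO2 endpoints are derived from the pulse-oximeter trend at its finest stored interval. If the trend is not stored, derive them from a log in which the blinded observer enters the start, stop and lowest value of every episode below 90%. Limit the 3-min readings to the periodic vital-sign summaries.

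A sensitivity analysis that counts airway rescue for SpO2 below 90% as an event is optional. It would require each rescue step to be logged and changes nothing in clinical management.

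The cost is a sentence or two in the protocol and one export or log per patient. Recruitment began on 9 March 2022 (section 2.1), so stored trends for patients already enrolled should be retrieved where available. Where none exists, the report should say which patients were classified from which source.
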